### Statistical analysis

For the primary target, out of all available proteomics and metabolomics data, possible predictors for the differentiation between AIS and ICH are extracted by means of logistic regression. Similar to the selection process for the secondary target, predictors will be chosen to differentiate between AIS (and ICH) on the one side and SM on the other side.

For both targets of this “discovery phase,” all predictors will be tested individually to assess their prediction quality (Hosmer). Predictors with a “significant contribution” (that is, a *p*-value in the Chi-squared test with *p* < α = 0.20) will be acknowledged as suitable candidates and further investigated in the combined Phases 2 and 3 (“Derivation Phase” and “Validation Cohort”) taking place at a later phase of the biomarker project with a new sample.

Additionally, sensitivity, specificity, and predictive values will be tested for potential biomarkers.

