### Hypotheses

#### Primary hypothesis

One or a group of different blood biomarkers enables the differentiation between AIS and ICH in patients with acute stroke with sufficient sensitivity, specificity, and predictive values.

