**Figure 2 F2:**
[figure not shown]
Conduction of the study. Procedure for including patients in the study is shown in chronological order from left to right. Boxes in red describe procedures during routine emergency treatment, and boxes in blue describe study-specific procedures. Blood samples will only be analyzed in cases where the patient or legal representative gives written informed consent. The blood sample is temporarily stored in the fire or rescue station and later in a biobank.

In contrast to many other studies, we plan to use a broad spectrum of potential biomarkers using a so-called “multi-omics” approach [proteins (proteomics), genes (genomics), ribonucleic acid (RNA [transcriptomics]), and metabolites (metabolomics)]. A second study-related blood sample will be collected from AIS and ICH patients 20 to 60 min after the collection of the first sample, usually done upon the patient's arrival at the hospital, the study allows for the examination of concentration changes and kinetics in the early phase. We plan to include 300 patients in this study. The study will be initially implemented at one MSU (STEMO 3600) and then rolled out to the other two MSUs. Universal trial number (UTN): U1111–1258-2477.

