#### Sample size

In this explorative study (“discovery phase”), no decisive sample size calculation can be performed, as the effect size of the parameters with respect to predicting to which group the patients belong will become clear only through and at the end of this study. Thus, the envisaged sample sizes will be used to determine the effects that can be detected with them (see next section).

Since, for all patients, the ultimate diagnosis (AIS, ICH, or SM) is known only in retrospect, patients will be included until the targeted sample sizes of all groups are completed or the anticipated study end is reached.

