### Power analysis

For the primary target, the data from 80 AIS and 80 ICH patients will be used. Given the elevated alpha = 0.20 used here, the standard value of beta = 20% (corresponding to a power of 80%), and the use of the Chi-squared test, the sample will be sufficient to detect all large, medium, and small effects of w ≥ 0.17 (Cohen's d ≥ 0.30). For the secondary target, for which data from 40 AIS (taken as a random sample out of the pool of 80 patients) and 40 SM patients will be used, the numbers will suffice to detect large, medium, and some smaller effects with w ≥ 0.24 (Cohen's d ≥ 0.40) and thus all effects with a minimally clinically important difference (MID).

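### Predictive values taken directly from the planned 1:1 analysis sets would reflect a 50% share set by design, not the mix met on MSU deployments, although both hypotheses are worded in terms of predictive values

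*Protocol article*

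**What the plan says.** The Primary hypothesis of the protocol article is that one or several markers separate AIS from ICH "with sufficient sensitivity, specificity, and predictive values". The Secondary hypothesis uses the same criterion for acute stroke against stroke mimics (SM).

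The Statistical analysis section screens each predictor separately at a p-value below 0.20. It then adds that "sensitivity, specificity, and predictive values will be tested for potential biomarkers", without naming the patients used or the share of each diagnosis assumed.

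The analysis sets appear under Power analysis: "For the primary target, the data from 80 AIS and 80 ICH patients will be used", and for the secondary target "40 AIS (taken as a random sample out of the pool of 80 patients) and 40 SM patients will be used". The second set contains no ICH patients, although the Secondary hypothesis speaks of acute stroke and the Statistical analysis section places ICH beside AIS in that contrast.

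On recruitment, the Sample size section says that "patients will be included until the targeted sample sizes of all groups are completed or the anticipated study end is reached", the diagnosis being known only afterwards. The Study design section adds: "We plan to include 300 patients in this study".

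The study is described as a discovery phase. Candidates pass to later derivation and validation phases that use a new sample.

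**The concern.** Sensitivity and specificity are conditional on the diagnosis, so a 1:1 mix does not in itself distort them. PPV and NPV are conditional on the marker result and depend directly on how common each diagnosis is. In a set of 80 AIS and 80 ICH patients, the ICH share is 50% because the plan chose it. A predictive value read off that set answers a question about a population that MSU crews may never meet.

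This matters because the article uses predictive values as a yardstick. Both hypotheses name them. The Discussion judges an earlier panel insufficient on a positive predictive value of 80.8%, and lists inadequate predictive values among the limits of single markers. A raw PPV of about 82% from the 1:1 set would look comparable with that benchmark, yet could correspond to a far lower figure in the field.

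A secondary matter is that the accuracy figures would come from the same patients in whom the markers are selected, which tends to make them optimistic.

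**Working it through.** **Inputs.** From Power analysis: 80 AIS and 80 ICH; 40 AIS and 40 SM. From the Discussion: GFAP sensitivity (se) 75% and specificity (sp) 84% for ICH, used here only as an illustration. The ICH share p among strokes is not given in the article, so it is an assumption and is shown over a range.

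**The plan's own figure.** For a Chi-squared test with 1 degree of freedom, noncentrality N·w², alpha 0.20 and power 80%, N = 160 gives w = 0.168 and N = 80 gives w = 0.237. The stated 0.17 and 0.24 are reproduced. The power statement therefore rests on sets of 160 and 80 patients, which the article divides 80:80 and 40:40.

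**What a direct calculation would give.** With se 75%, 80 ICH patients yield 60 marker-positive and 20 marker-negative. With sp 84%, 80 AIS patients yield 67.2 negative and 12.8 positive on average. PPV = 60/72.8 = 82.4%. NPV = 67.2/87.2 = 77.1%.

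**The same marker at other shares.**

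PPV = se·p / [se·p + (1 − sp)(1 − p)]

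NPV = sp(1 − p) / [sp(1 − p) + (1 − se)p]

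| ICH share among strokes | PPV for ICH | NPV for ICH |
|---|---|---|
| 50% (analysis set) | 82.4% | 77.1% |
| 30% (assumed) | 66.8% | 88.7% |
| 20% (assumed) | 54.0% | 93.1% |
| 10% (assumed) | 34.2% | 96.8% |
| 5% (assumed) | 19.8% | 98.5% |

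For example, at 10%: PPV = 0.075/(0.075 + 0.144) = 0.342, and NPV = 0.756/(0.756 + 0.025) = 0.968. ICH remaining among marker-negative patients is 1 − NPV: 23% in the 1:1 set and 3% at a 10% share.

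**A bound from the plan's own numbers.** If 300 patients were enrolled and all targets met, with at least 80 ICH and 40 SM, there could be at most 300 − 80 − 40 = 180 AIS. The ICH share among strokes would then be at least 80/260 = 31%, close to the 30% row. The plan does not promise this, because recruitment may end before the targets are met.

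**Secondary target.** Using the same se and sp purely for illustration, with stroke as the positive class, PPV/NPV are 82.4%/77.1% at the designed 50% stroke share, 66.8%/88.7% at 30% and 91.6%/59.0% at 70%. The direction of the error depends on whether strokes or mimics are commoner.

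**Same-data optimism.** Pure-noise markers were simulated, with the best cut-off and direction chosen in the same patients (200 runs, an assumed 500 markers). Their true PPV at 1:1 is 50%. Those passing p < 0.20 showed an apparent PPV of about 61% at 80+80 and 65% at 40+40. The best of 18 noise markers (18 being the number the Biomarkers section names) showed about 63% and 67%. The article describes no cut-off rule, so these figures apply only if a cut-off is chosen in this way.

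**The case against.** The strongest reply is that the article never says predictive values will be raw proportions from the 1:1 sets. Those sets appear only under Power analysis, and the choice between raw proportions and Bayes' formula is commonly left to an analysis plan. That is fair, and the absence of a formula is not the point here. The point is that two things the article does fix, 1:1 sets and hypotheses worded on predictive values, do not fit together unless something is added.

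Four stronger readings are tempting, and the documents do not support them:

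- *Recruitment is forced to 1:1.* The Sample size section closes no group once it is filled. Only the analysis sets are 1:1, so the enrolled mix stays available for re-weighting, subject to consent and a successful blood draw.
- *The figures will be wrong for every prehospital population.* The article gives no ICH share, and every share below 50% used here is an assumption.
- *The error always flatters the marker.* For ICH shares below 50%, PPV is overstated but NPV is understated. The Conclusions call ruling out ICH the most important objective, and for that quantity the 1:1 figure is pessimistic.
- *Marker selection is compromised.* The only stated selection rule is p < 0.20. Predictive values are an addition to it, and no threshold for sufficiency is set.

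On optimism, the later phases with a new sample are the right safeguard for the final claim. They do not correct figures reported from this phase, and the article does not say that those figures are provisional.

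**Conclusion.** The concern holds for predictive values as reported from this phase and as used to judge the two hypotheses. Computed directly in the planned sets, PPV and NPV describe a 50% share set by design. For a marker with 75% sensitivity and 84% specificity, PPV for ICH falls from 82% to 54%, 34% or 20%, and NPV rises from 77% to 93%, 97% or 98.5%, at assumed ICH shares of 20%, 10% or 5%. At 30%, near the lower bound implied if all targets were met within 300 patients, the pair is 67% and 89%.

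The conclusion assumes that the accuracy figures come from the sets under Power analysis, the only ones the article gives, and that sensitivity and specificity stay constant as the mix changes. It does not extend to the candidate screen, nor does the 1:1 mix bias sensitivity or specificity. Same-data optimism is real but secondary.

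**What to change.** In the Statistical analysis section, state that PPV and NPV are not taken as raw proportions from the 1:1 sets. They are calculated by Bayes' formula from the estimated sensitivity and specificity and the AIS/ICH/SM mix among all enrolled patients with a final diagnosis. Add a table over a range of ICH and SM shares, and report likelihood ratios. For the secondary target, say whether the contrast is AIS or all stroke against SM, since the planned set holds no ICH patients.

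Alternatively, defer predictive values to the validation cohort and reword both hypotheses so that this phase is judged on sensitivity and specificity only.

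In either case, label accuracy figures from this phase as provisional, or correct them for optimism with a bootstrap that repeats the marker selection and any cut-off choice.

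The cost is a little more analysis work and no new data. If the ICH share is below 50%, the reported PPV for ICH will be lower and the NPV higher than the raw figures.

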### Power analysis

For the primary target, the data from 80 AIS and 80 ICH patients will be used. Given the elevated alpha = 0.20 used here, the standard value of beta = 20% (corresponding to a power of 80%), and the use of the Chi-squared test, the sample will be sufficient to detect all large, medium, and small effects of w ≥ 0.17 (Cohen's d ≥ 0.30). For the secondary target, for which data from 40 AIS (taken as a random sample out of the pool of 80 patients) and 40 SM patients will be used, the numbers will suffice to detect large, medium, and some smaller effects with w ≥ 0.24 (Cohen's d ≥ 0.40) and thus all effects with a minimally clinically important difference (MID).

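### The bracketed Cohen's d values in the power statement (0.30 and 0.40) are not equivalent to the printed w values; they should be about 0.34 and 0.48

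*Protocol article*

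**What the plan says.** The Power analysis section of the protocol article sets the error rates ("Given the elevated alpha = 0.20 used here, the standard value of beta = 20% (corresponding to a power of 80"%) and names the method: "and the use of the Chi-squared test". For the primary target, 80 AIS against 80 ICH patients, it concludes that "the sample will be sufficient to detect all large, medium, and small effects of w ≥ 0.17 (Cohen's d ≥ 0.30"). For the secondary target, 40 AIS against 40 stroke-mimic patients, it says the numbers suffice for large, medium and "some smaller effects with w ≥ 0.24 (Cohen's d ≥ 0.40"), "and thus all effects with a minimally clinically important difference (MID").

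The Statistical analysis section uses the same alpha for selecting candidates, "in the Chi-squared test with *p* < α = 0.20", and says that "all predictors will be tested individually to assess their prediction quality (Hosmer"). The Sample size section explains that no decisive calculation is possible in a discovery phase, so the planned group sizes are instead used to work out which effects they can detect.

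**The concern.** Each sentence gives one detectable effect on two scales, w and d, as if the two were the same threshold. With two groups of equal size, d is roughly twice w, so 0.17 should sit beside a d near 0.34 and 0.24 beside a d near 0.48. Both printed d values are smaller than that, which makes the sample look more sensitive than it is on the d scale.

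The Sample size section makes these detectable effects the only quantitative support for the group sizes. The secondary figure also leads directly into the claim about minimally important differences. Someone planning the later derivation and validation phases from the d values would start from thresholds that this sample does not detect with 80% power.

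**Working it through.** **Inputs.** From Power analysis: alpha 0.20, power 80%, chi-squared test, groups of 80/80 (N = 160) and 40/40 (N = 80). The degrees of freedom are not stated. I take 1, because Statistical analysis says predictors are tested one at a time; step 1 supports this choice.

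**1. Reproduce the printed w.** For a non-central chi-squared test with 1 df, alpha 0.20 and power 0.80, the required non-centrality is λ = 4.503, and w = √(λ/N).
- N = 160: √(4.503/160) = 0.168, printed as 0.17. Power at w = 0.17 is 80.8%.
- N = 80: √(4.503/80) = 0.237, printed as 0.24. Power at w = 0.24 is 80.7%.

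Both reproduce, which identifies the calculation behind them: 1 df, non-directional alpha 0.20, total N of 160 and 80.

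**2. Convert w to d.** For two equal groups, d = 2w/√(1 − w²).
- Primary: 2 × 0.168/√(1 − 0.168²) = 0.34.
- Secondary: 2 × 0.237/√(1 − 0.237²) = 0.49 (0.488 from the unrounded w).

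The simpler d = 2w gives 0.34 and 0.47. Starting from the rounded 0.17 and 0.24, the full conversion gives 0.345 and 0.494.

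**3. Cross-check with a two-sample comparison of means** (SD 1, two-sided 0.20). d = (1.2816 + 0.8416) × √(2/n).
- n = 80: 2.1232 × √(2/80) = 0.336; non-central t also gives 0.336.
- n = 40: 2.1232 × √(2/40) = 0.475; non-central t gives 0.477.

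**4. Work backwards from the printed d.** w = d/√(d² + 4).
- d = 0.30: 0.30/√4.09 = 0.148, not 0.17.
- d = 0.40: 0.40/√4.16 = 0.196, not 0.24.

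**5. Power at the printed d.** Φ(d/√(2/n) − 1.2816).
- d = 0.30, n = 80: Φ(1.897 − 1.282) = Φ(0.616) = 73.1% (t: 73.0%; chi-squared at w = 0.148: 72.5%).
- d = 0.40, n = 40: Φ(1.789 − 1.282) = Φ(0.507) = 69.4% (t: 69.2%; chi-squared at w = 0.196: 68.3%).

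The type II error at those effects is therefore about 27% and 31%. For 80% power, n = 2 × 2.1232²/d² gives 101 per group at d = 0.30 and 57 per group at d = 0.40.

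**6. Could another reading give 0.30 and 0.40?**

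| Reading | Primary d | Secondary d | Does it fit? |
|---|---|---|---|
| One-sided alpha 0.20 | 0.27 | 0.38 | No: w would be 0.133 and 0.188 |
| Logit conversion of w | 0.37 | 0.53 | No: further away |
| Probit conversion of w | 0.42 | 0.60 | No: further away |
| 80 AIS against 40 mimics | not applicable | 0.41 | No: text fixes 40/40, and N = 120 gives w = √(4.503/120) = 0.194 |
| Rounding to one decimal | 0.3 | 0.5 | No: only truncation gives 0.3 and 0.4 |

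**The case against.** The strongest reply is that w is the effect size that belongs to the stated chi-squared test, and at the printed w the power is 80% as claimed. The main statement is therefore correct and only the bracketed translation fails. That stands. A reader might infer from the 73% and 69% that the study as a whole falls short of its 80% power. The document does not support that: those figures apply only at d = 0.30 and d = 0.40.

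A second reply is that nothing was derived from d. The group sizes were set in advance, and the screening rule works on a p-value. That also stands, and it limits the severity.

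A third is that a one-sided alpha of 0.20 would make both d statements true, if conservative: detectable d would be 0.27 and 0.38, with power of about 85% and 83% at the printed values. So it would be wrong to say that no choice of sidedness makes the d statements true. The one-sided reading fails for a narrower reason: the stated chi-squared test is non-directional, and the printed w fit only that version.

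Finally, a reader might conclude that the claim about minimally important differences is false. That does not follow. The article states no value for the difference, and a condensed article may leave it to the full protocol. If it is meant on the d scale, the correction matters only for a value between 0.40 and about 0.48; for anything larger the claim survives.

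**Conclusion.** The two bracketed d values are wrong as equivalents of the printed w. They should be about 0.34 rather than 0.30, and about 0.48 (0.47 to 0.49 by conversion) rather than 0.40. Both errors flatter the sample. Power at the printed d is about 73% and 69%, shortfalls of about 7 and 11 percentage points from the 80% stated.

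This rests on 1 df, which is inferred but confirmed by the reproduced w, on equal groups as stated, and on a standard conversion or a two-sample comparison of means. The logit and probit conversions give still larger d, so the direction does not depend on the choice.

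The severity is moderate. The error is more than clerical, because these detectable effects are the only quantitative support for the group sizes. It does not change enrolment, alpha, the test or the p < 0.20 rule.

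**What to change.** In Power analysis, do one of the following:
- restate the pairs as w ≥ 0.17 (Cohen's d ≥ 0.34) and w ≥ 0.24 (Cohen's d ≥ 0.48), and name the conversion used; or
- keep d of 0.30 and 0.40, separate them from the w values, and state power of about 73% and 69% at those effects.

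Tie the clause on minimally important differences to the corrected secondary d. Keep it only if the intended difference, on the d scale, is at least about 0.48; otherwise reword it.

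The cost is a correction to two sentences. The stated sensitivity becomes slightly less favourable, and no group size or analysis changes.

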**Methods and analysis:**

We plan a prospective, observational study involving 300 patients with suspected stroke and symptom onset of ≤4.5 h before the collection of biomarkers. Study participants will be recruited from three sites in Berlin, Germany during MSU deployments. The focus of the study is the collection of blood samples from participants at the prehospital scene and from participants with AIS or ICH at a second-time point. All samples will be analyzed using targeted and untargeted analytical approaches. Study-related information about participants, including medical information and discharge diagnoses from the subsequent treating hospital, will be collected and documented in an electronic case report form (eCRF).

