#### Secondary hypothesis

One or a group of different blood biomarkers enables the differentiation between acute stroke and SM in patients with suspected stroke with sufficient sensitivity, specificity, and predictive values. The kinetics of biomarkers in the early phase of a stroke may improve discriminatory power.

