#### Primary and secondary targets

As this is an explorative study (discovery phase), the primary target is to identify a single blood-based biomarker, or a panel of biomarkers, with strong differentiation between the AIS and the ICH groups, i.e., to identify candidates for a prediction model that will then be tested and refined in a subsequent study.

The same is true for the secondary target, namely, to identify a single blood-based biomarker or, again, a group of markers with great differences between stroke and SM patients.

To this end, the absolute values of blood biomarkers and their kinetics in AIS and ICH patients will be determined. We expect a change in the concentration of biomarkers over time in the acute phase after AIS and ICH patients due to vascular injury and subsequent neuronal cell injury, whereas we expect no such changes in SM patients.

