#### Secondary analysis

The prehospital distinction between patients with a stroke and SM without cerebral imaging and solely based on one or a combination of blood biomarkers.

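### The Power analysis section fixes the secondary comparison as a random 40 of 80 AIS patients against 40 SM patients, which contradicts the stroke-versus-SM target stated elsewhere and leaves out 120 available stroke patients

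*Protocol article*

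**What the plan says.** Four sections of the protocol article describe the secondary question as stroke against SM:

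- Secondary hypothesis: a marker or group of markers "enables the differentiation between acute stroke and SM in patients with suspected stroke".
- Primary and secondary targets: a single marker or "a group of markers with great differences between stroke and SM patients".
- Secondary analysis: "The prehospital distinction between patients with a stroke and SM without cerebral imaging".
- Statistical analysis: "predictors will be chosen to differentiate between AIS (and ICH) on the one side and SM on the other side".

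The Definitions section lists both ischemic stroke and intracerebral hemorrhage under stroke.

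The Power analysis section describes a different comparison. For the secondary target, "data from 40 AIS (taken as a random sample out of the pool of 80 patients) and 40 SM patients will be used". ICH patients are not mentioned there. The preceding sentences of the same section read "For the primary target, the data from 80 AIS and 80 ICH patients will be used" and "Given the elevated alpha = 0.20 used here". The detectable effect given for the secondary target is w ≥ 0.24, also expressed as d ≥ 0.40.

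On assays, the abstract's Methods and analysis paragraph says: "All samples will be analyzed using targeted and untargeted analytical approaches".

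**The concern.** An analyst cannot follow both the Statistical analysis and the Power analysis sections. If the latter governs, three things follow.

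1. A result reported as stroke versus SM would describe AIS versus SM only. The protocol's own Discussion cites GFAP as higher in ICH than in AIS and non-stroke patients, so a marker that moves mainly in ICH is a realistic case.
2. Half of the AIS patients and all of the ICH patients are left out although their samples are assayed and used for the primary target. No reason is given. Logistic regression does not need equal groups, so cutting the larger group down to 1:1 only loses precision.
3. Which AIS patients enter is left to a random draw, so the candidate list for the secondary target depends partly on that draw.

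This matters because only predictors that pass the p < 0.20 screen go forward to the later derivation and validation phases.

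**Working it through.** **Inputs.** From the Power analysis section: 80 AIS, 80 ICH, 40 SM, a random 40 of the AIS for the secondary target, alpha 0.20, power 80%, chi-squared test. The degrees of freedom are not stated; I assume 1, which corresponds to a two-sided test. Normal quantiles: z(0.90) = 1.2816 and z(0.80) = 0.8416, sum 2.1232.

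**Step 1. Reproduce the plan's figure.** Approximately w = 2.1232/√N.
- N = 80: 2.1232/√80 = 0.237 (noncentral chi-squared also gives 0.237). The plan states 0.24, and power at w = 0.24 is 80.7%.
- N = 160 (primary target): 0.168. The plan states 0.17.
- N = 120 or 200 would give 0.194 or 0.150.

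The stated w for the secondary target therefore belongs to 40 + 40 patients. That comparison is the one actually powered; it is not loose wording.

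**Step 2. Count what is left out.** Stroke patients in the primary target: 80 + 80 = 160. Used for the secondary target: 40. Left out: 40 AIS + 80 ICH = 120, or 75%.

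**Step 3. Detectable d.** d = 2.1232 × √(1/n₁ + 1/n₂), with 40 SM throughout.

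| Stroke group | √(1/n₁ + 1/40) | Detectable d | Power at d = 0.40 |
|---|---|---|---|
| 40 AIS (as planned) | 0.2236 | 0.475 | 69% |
| 80 AIS | 0.1936 | 0.411 | 78% |
| 80 AIS + 80 ICH, unweighted | 0.1768 | 0.375 | 84% |

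With the t distribution the three values of d are 0.477, 0.412 and 0.376, rounded to 0.48, 0.41 and 0.38. The last row assumes the same effect in AIS and ICH.

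**Step 4. Weighted pool.** If AIS has weight s and ICH 1 − s, the standard error in SD units is √([s² + (1 − s)²]/80 + 1/40). The documents give no shares, so s = 0.70 to 0.90 is an assumption.
- s = 0.70: √(0.58/80 + 0.025) = 0.1796, d = 0.38, power at d = 0.40 is 83%.
- s = 0.90: √(0.82/80 + 0.025) = 0.1877, d = 0.40, power 80%.

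**Step 5. A marker shifted only in ICH** (illustrative assumption: 1 SD; simulated).
- 40 AIS vs 40 SM: selected 20% of the time, which is alpha.
- All 160 stroke patients vs 40 SM, unweighted: 92%.
- 80 ICH vs 40 SM: over 99%.

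In a weighted pool the mean shift is only 1 − s. By the normal approximation, the chance of selection is Φ(0.30/0.1796 − 1.2816) ≈ 65% at s = 0.70. At s = 0.90 it is Φ(0.10/0.1877 − 1.2816) + Φ(−0.10/0.1877 − 1.2816) ≈ 26%. A weighted pool alone would therefore not recover such a marker; the separate ICH-versus-SM contrast does.

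**Step 6. Dependence on the draw** (simulated: 80 AIS, the same 40 SM, p < 0.20). For a true d = 0.40, two independent draws of 40 from the 80 AIS disagree on selection about 20% of the time; two non-overlapping halves disagree 29% of the time. For independent draws the figure falls to 8% at d = 0.6 and about 1.4% at d = 0.8.

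**The case against.** **ICH is not excluded everywhere.** The Statistical analysis section names ICH, in parentheses, on the stroke side. A reader might infer that the trial never tests stroke against SM. The documents do not support that: two sections disagree, and which one governs is not stated. This stands, and it makes the point a contradiction to be resolved.

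**The plan meets its own w.** A reader might take the 69% power at d = 0.40 as proof that subsampling leaves the study underpowered against its target. It is not. At w = 0.24, power is 80.7%. The 69% arises largely because d = 0.40 does not match w = 0.24: with equal groups, d = 2w/√(1 − w²) = 0.48/0.971 = 0.49. That mismatch is a separate matter. The loss from subsampling is the difference between the rows of the table, not the 69% itself.

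**An ICH marker is not lost altogether.** It is tested in the primary AIS-versus-ICH comparison with all 80 ICH patients, and GFAP is measured as a named candidate in any case. This stands. Only the evaluation of such a marker for stroke versus SM is affected.

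**This is a discovery screen.** Random subsampling does not bias the AIS-versus-SM estimate, candidates are to be examined again in a new sample, and the stated aim is markers with large differences, for which the draw matters little. This also stands and lowers the severity. It gives no reason to discard measured data, since a screen at alpha 0.20 is meant to avoid missing candidates.

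**Pooling brings a modest gain.** Adding ICH to the full AIS group moves d only from 0.41 to 0.38–0.40. That is correct. The main reason to include ICH is that the target names stroke.

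**Conclusion.** The concern holds as a contradiction between the Power analysis section and the four sections that state the secondary target as stroke versus SM, together with an unexplained loss of data. If the Power analysis governs, the secondary result speaks to AIS versus SM only, and a marker shifted only in ICH passes that screen no more often than chance.

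Using all measured stroke patients lowers the detectable d from 0.48 to 0.38 (unweighted, common effect in AIS and ICH) or to 0.38–0.40 (AIS share assumed to be 70–90%). All 80 AIS alone give 0.41. The common-effect assumption behind the 0.38 and the ICH-only marker are two different scenarios, and a given marker cannot satisfy both. The dependence on the draw, about 20% at d = 0.40, applies to modest effects and fades for large ones.

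Severity is moderate: this is the secondary target of an exploratory study, and the primary comparison is untouched.

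**What to change.** Drop the random sample of 40 AIS patients. In the Power analysis and Statistical analysis sections, state that:

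- all AIS and all ICH patients are compared with all SM patients in logistic regression;
- AIS versus SM and ICH versus SM are each reported separately;
- the weighting of AIS and ICH is given for any pooled sensitivity or predictive value, because 80:80 is a design ratio and not the mix met in practice;
- the detectable effect is restated for the comparison actually made.

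If only AIS versus SM is intended, rename the secondary hypothesis, target and analysis to say so, and still use all 80 AIS patients.

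The cost is two further contrasts, a stated weighting rule and a revised power sentence. If all samples are analyzed, as the abstract says, no extra assays are needed.
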